Serological markers: NAFLD fibrosis score, FIB-4, and Hepamet score. Several predictive models of advanced fibrosis are based on formulas using clinical and analytical parameters.FibroScan and CAP: Transitional elastography or FibroScan is the most widespread technique in the non-invasive diagnosis of liver fibrosis. It measures by ultrasound the speed of propagation of low-frequency waves through the liver parenchyma. CAP is an application of FibroScan that measures the degree of attenuation of the ultrasound wave transmitted through the liver proportional to the amount of liver fat.DEMILI: Computerized optical analysis software of conventional liver magnetic resonance images that determines a number of optical biomarkers that allow the detection of NASH and the prediction of significant fibrosis.Metabolomic profile: Owl-liver. Serum analysis for the determination of fatty liver disease and NASH diagnosis based on the determination of more than 500 serum metabolites by liquid chromatography coupled to mass spectrometry. Using the method developed by the company OWL (ONE WAY LIVER, S.L., Derio -Vizcaya-).Changes in lipid parameters: Cholesterol, LDL, HDL, and triglyceridesVariation in body weight.Changes in endothelial dysfunction biomarkers: ICAM-1, VCAM-1, E-selectin, P-selectin, angiopoietin-2, endocan, RBP4, OPG, and ADMA.Changes in macrophage activation biomarkers: Gal 3, Gal-3BP, sCD163, and sCD14.Changes in the glucose homeostasis biomarkers and insulin resistance: glucose, hemoglobin A1c (HbA1c), homeostatic model assessment for insulin resistance (HOMA-IR), adiponectin, retinol-binding protein 4 (RBP-4), monocyte chemoattractant protein-1 (MCP-1), plasminogen activator inhibitor-1 (PAI-1), leptin, resistin, visfatin, and apelin.Changes in the intestinal microbiota by sequencing the 16S rRNA in stool samples.Changes in inflammation biomarkers: fibrinogen, hs-CRP, haptoglobin, TNF-alpha, IL-6, and IL-1β.Changes in serum expression of incretins: GLP-1, GIP, and YY peptide.Changes in the cardiovascular risk profile.

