### Statistical methods

#### Statistical methods for primary and secondary outcomes {20a}

Data will be analyzed using SPSS version 19. A descriptive baseline and end-of-follow-up analysis (week 96) of the data will be performed using the mean and standard deviation or the median and range where appropriate for quantitative data and percentage for qualitative data. Quantitative variables will be compared with Student’s *t* test and qualitative variables will be compared with *X*^2^. When variables do not follow a normal distribution, non-parametric tests should be used. Paired data tests will be used to analyze baseline and 96-week results.

All changes in efficacy parameters endpoints will be analyzed in an intention-to-treat and per-protocol analysis and grouped by randomized treatment.

The Intent-to-Treat (ITT) population will include all subjects randomized to treatment. The per-protocol (PP) population will be a subset of the ITT population, excluding subjects that violate key protocol criteria, with the exact list of exclusion reasons to be included in the statistical analysis plan (SAP).

The primary efficacy endpoint, by histopathological improvement of fibrosis by at least 1 stage without any worsening of NASH, and histopathological resolution of NASH without any worsening of the stage of fibrosis will be conducted on the intention-to-treat (ITT) population; so all randomized subjects will be included in the primary analysis.

Secondary endpoints analyzed by descriptive statistics and inferential statistics will include ANOVA. Non-parametric tests may be utilized such as Wilcoxon rank-sum.

For all tests, we will use 2-sided *p* values with alpha < 0.05 level of significance.

All safety variables (i.e., adverse events, laboratory data, vital signs, and ECG) will be summarized by treatment for all patients of the safety set. Descriptive statistics using appropriate summary statistics will be calculated for quantitative safety data as well as for the difference to baseline, when appropriate. In addition, a shift table describing out-of-normal range shifts will be provided for clinical laboratory results.

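### The test for each continuous secondary marker is left to depend on whether its data appear normal; one baseline-adjusted analysis, on the log scale for concentrations, should be named in advance

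*Protocol article*

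**What the plan says.** All statements on method are in the protocol article, Statistical methods for primary and secondary outcomes {20a}.

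- Default tests: "Quantitative variables will be compared with Student’s *t* test and qualitative variables will be compared with" a chi-squared test.
- Condition: "When variables do not follow a normal distribution, non-parametric tests should be used".
- Secondary endpoints, later in the same section: "Secondary endpoints analyzed by descriptive statistics and inferential statistics will include ANOVA", followed by "Non-parametric tests may be utilized such as Wilcoxon rank-sum".
- Summaries: "using the mean and standard deviation or the median and range where appropriate for quantitative data".
- What is analysed: "All changes in efficacy parameters endpoints will be analyzed in an intention-to-treat and per-protocol analysis and grouped by randomized treatment".

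The Secondary outcomes section words most laboratory markers as changes, for example "Changes in inflammation biomarkers: fibrinogen, hs-CRP, haptoglobin, TNF-alpha". Lipids, adhesion molecules, adipokines, gut hormones and bone markers are listed in the same way. The article does not say whether a change is absolute, relative or logarithmic. It names no normality criterion and gives no SD, baseline correlation, expected effect or power for any marker.

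**The concern.** There are two difficulties.

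First, the data decide which analysis is reported. A t test is tied to a difference in means and a rank test is not, so two similar markers, or one marker in the ITT and per-protocol sets, may be reported on different footings. The section also states the rule twice with different force: a rank test *should* replace the t test under non-normality, then *may* be used beside ANOVA.

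Second, the rule is the only remedy offered for skewness, and it does not reach the cause when the variable is a raw change. For a positive marker that moves proportionally, raw change = baseline × (ratio − 1). Patients with high baselines then dominate the spread, and ranking the raw change keeps that noise.

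At stake are precision and readability of the secondary comparisons. The Hypotheses section expects ESG to do at least as well as surgery on weight, metabolic comorbidities and histology. In 30 patients, a missed difference in a metabolic marker is easily read as equality unless an interval shows what has not been excluded.

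**Working it through.** **The plan's own figure.** The article gives no marker power to reproduce. Its only sample-size figure, in Sample size {14}, concerns NASH resolution: 85% v 25%, two-sided alpha 0.01, power 90%, 7% loss. With unpooled variance, n per arm = (2.576 + 1.282)² × (0.85×0.15 + 0.25×0.75) / 0.60² = 14.88 × 0.315 / 0.36 = 13.02, rounded up to 14. Then 14 × 1.07 = 14.98, so 15 per arm and 30 in total. This reproduces the figure. It supplies the 15 per arm used below and says nothing about marker power.

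**Inputs.** From the documents: 15 per arm, 1:1 allocation, two-sided 0.05. Assumed, because the documents give none of them:
- log-normal markers with log-SD 0.3, 0.5 and 0.7 (CV = √(exp(s²) − 1) = 31%, 53% and 80%);
- correlation 0.6 between log baseline and log week-96 value;
- a proportional arm effect sized so that a t test on log(week 96 / baseline) has about 80% power;
- a fall common to both arms of 0 or 0.3 on the log scale (exp(−0.3) = 0.74, a 26% fall);
- normality judged by Shapiro-Wilk at 0.05 in each arm; if either arm rejects, Wilcoxon rank-sum, otherwise Student's t.

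**Stability of the choice.** The rank test is selected in about 20-26%, 39-51% and 61-74% of trials at log-SD 0.3, 0.5 and 0.7. The true distribution is the same within each setting; only the sample differs. Under the same kind of rule, dropping one patient per arm, as a per-protocol set might, changes the chosen test in 8-9% of trials.

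**Power of the rule on raw change** (log-SD 0.3 / 0.5 / 0.7), against about 80% for the log ratio:

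| Common fall (log) | Tested arm | Power of rule, % | Loss, points |
|---|---|---|---|
| 0 | higher | 81 / 81 / 78 | −1 / −1 / 2 |
| 0 | lower | 70 / 64 / 56 | 10 / 16 / 24 |
| 0.3 | higher | 70 / 70 / 72 | 10 / 10 / 8 |
| 0.3 | lower | 52 / 46 / 41 | 28 / 34 / 39 |

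The loss is therefore about 0-40 points. In a wider grid with 14 per arm, log-SD up to 1.0 and a common fall of 0.5, it reaches about 54 points.

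**Why direction matters.** Ratios of 1.61 and 0.62 are mirror images on the log scale. On the raw scale they shift the median by 0.61 and 0.38 of baseline. After a common fall to 0.74 the shifts are 0.74 × 0.61 = 0.45 and 0.74 × 0.38 = 0.28.

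**Where the loss comes from.**
- Not from switching. At log-SD 0.8, correlation 0.5, common fall 0.3, tested arm lower and 14 per arm, power on raw change is 0.31 for the rule, 0.24 for always-t and 0.31 for always-Wilcoxon. It is 0.68 for a t test on log change and 0.78 for log-scale ANCOVA.
- From the scale. The same t/rank rule applied to week 96 / baseline has 76-81% power against 79-82% for the log ratio, a loss of 0-3 points. Applied to final values, it loses about 0-4 points against a log-scale t test of the same final values.
- From the missing baseline adjustment. With equal log-SDs at both times, the residual variance of log ANCOVA relative to that of log change is (1 + ρ)/2 = 0.8 at ρ = 0.6. The standardised effect rises by 1/√0.8 = 1.118. From 1.96 + 0.84 = 2.80 it becomes 3.13, and Φ(3.13 − 1.96) = Φ(1.17) = 0.88. Simulation gives 86-88%.

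**Type I error.** The rule rejects in 4.4-5.4% of null trials, so the level holds.

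**The case against.** The strongest case against runs as follows. The article never says that changes are raw differences, and scale and transformation marker by marker are normally left to the SAP, which is not shown. Non-normality could be judged beforehand for each marker, since no test on the trial data is named. The simulation draws data from the model that its preferred analysis fits. The outcomes are secondary, in a 30-patient trial that claims no power for them, and most of the cytokines and adhesion molecules lie outside the stated hypothesis.

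Much of this stands. Silence on the scale is not a fault in a condensed article, so the power loss can only be conditional. The selection percentages depend on the Shapiro-Wilk assumption. For a truly normal marker (CV 10-30%) the existing rule loses little: 79-81% power against 80-85% for the log ratio.

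What does not fall away is the rule itself. It is a stated rule, not a gap. Section {20a} explicitly defers to the SAP only the list of per-protocol exclusion reasons, and it words the rank-test condition in two ways.

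A reader might infer that the t/rank switch costs a definite amount of power, say 15 to 28 points. The documents do not support this: they give none of the required inputs, such a figure is one slice of a much wider range, and either test used alone on raw change does no better. A reader might also infer that rank results will come without any effect size or interval. The article does not say so; it promises medians and ranges and is silent on intervals.

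**Conclusion.** The point holds as a weakness of the stated rule. It lets the data choose the test for each continuous secondary marker, and with 15 per arm that choice is unstable for skewed markers: the rank test is picked in roughly a fifth to a quarter of trials at log-SD 0.3, and in three fifths to three quarters at 0.7, under a Shapiro-Wilk gate.

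As a remedy for skewness it is ineffective if changes are raw. The conditional power loss is about 0-40 points against a log-ratio analysis, for log-normal markers with proportional effects, correlation 0.6 and a common log fall of 0 to 0.3. It is about 0-4 points if ratios or final values are compared. The cause is the raw scale and the lack of baseline adjustment. The primary histological endpoint and the type I error are untouched. The change is worth making because it is cheap and gives each marker one interpretable effect measure.

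**What to change.** In section {20a}, delete the normality condition and the later optional sentence on rank tests, and name one analysis before data are seen:

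- **Positive concentration markers** (lipids, glucose, insulin resistance, cytokines, adhesion molecules, hormones, bone markers): a linear model of log week-96 value on arm, log baseline and the diabetes stratum used in randomisation, reported as a ratio of geometric means with 95% CI, identically in the ITT and per-protocol sets.
- **Scores that can be zero or negative**: the same model on their own scale, with baseline adjustment.
- **Rank test**: a named sensitivity analysis only.

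An unadjusted t test on the log ratio would also fix the scale, but it is the weaker choice (about 80% against 86-88% power under the assumptions above).

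The cost is one paragraph of wording and no new data. Results are then read as ratios rather than unit changes, and undetectable values need a prespecified substitution rule.

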#### Trial design {8}

The TESLA-NASH study is a randomized, controlled, open-label, unicentric clinical trial with a sanitary product, designed to evaluate the efficacy of two gastric techniques (endoscopic versus laparoscopic) in the resolution of NASH without worsening liver fibrosis.
Experimental group: ESG + lifestyle modificationsControl group: LSG + lifestyle modifications

A total of 30 eligible participants will be randomly assigned (stratified by the presence or absence of type II diabetes mellitus) to the experimental group or the control group with a 1:1 ratio. The participants will be recruited at the Hospital Marqués de Valdecilla from June 2020 to June 2021.

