### Outcomes {12}

#### Primary outcome

Assessment of the efficacy of endoscopic vertical gastroplasty + lifestyle modification against laparoscopic vertical gastrectomy + lifestyle modification in the histological improvement of NASH from baseline to week 96 by the following:
Improvement of fibrosis in at least 1 stage without worsening of NASH.Resolution of NASH without worsening of fibrosis.

The resolution of NASH is defined as the histopathological disappearance of ballooning and the disappearance or persistence of minimal lobular inflammation (grade 0 or 1) using the NASH CRN scoring system with a type of general lesion that does not qualify as steatohepatitis. Worsening of fibrosis is defined as the progression of at least one stage.

For all the patients, a basal liver biopsy should be obtained prior to the execution of the therapeutic technique and a subsequent biopsy 96 weeks after the procedure should also be obtained.

To avoid inter-observer variability, the histological evaluation will be assessed by two local pathologists independently.

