##### Sample size {14}

Previous studies have shown a resolution of NASH in the 85% of patients undergoing a bariatric surgery (69.6% in gastric tubing surgery) and a resolution of 25% in patients with a lifestyle intervention. A bilateral ratio comparison test was used for sample size calculation with a confidence level of 99%, a statistical power of 90%, and an assumption of 7% loss. Obtained sample to observe differences is *n*=30 (15 per treatment arm).

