### Assignment of interventions: allocation

#### Sequence generation {16a}

Randomization will be carried out on all eligible subjects using a computer system. At the randomization visit, eligible subjects will be randomized 1:1 for the following groups:
Experimental group: ESG + lifestyle modificationsControl group: LSG + lifestyle modifications

Randomization will be stratified into 2 strata defined by diabetes status

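### Randomisation is stratified by diabetes and baseline values are collected, but the between-arm tests named use neither the stratum nor a baseline covariate: valid, but less efficient than a 30-patient trial could have

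*Protocol article*

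**What the plan says.** Sequence generation {16a} of the protocol article states that "Randomization will be stratified into 2 strata defined by diabetes status". Trial design {8} and the concealment section {16b} say the same. Baseline data are available: the Primary outcome section requires that "a basal liver biopsy should be obtained prior to the execution of the therapeutic technique", and the secondary outcomes are largely changes in weight, lipids, glucose measures and biomarkers.

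The statistical section {20a} then names the tests. Between arms, "Quantitative variables will be compared with Student’s *t* test and qualitative variables will be compared with *X*^2", with non-parametric alternatives. For baseline against follow-up, "Paired data tests will be used to analyze baseline and 96-week results". For the secondary outcomes, "Secondary endpoints analyzed by descriptive statistics and inferential statistics will include ANOVA", and Wilcoxon rank-sum is also mentioned. Tests are two-sided at "alpha < 0.05 level of significance". No diabetes term, stratified test or baseline covariate appears. Section {20b} on additional analyses reads as not applicable. The only item that {20a} hands to the statistical analysis plan is the list of reasons for per-protocol exclusion.

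**The concern.** Stratifying makes the arms alike on diabetes. If diabetes also predicts outcome, a test that ignores it leaves the between-stratum variation in its error term. The standard error is then too large and the test rejects too rarely under the null. Likewise, a t test on week-96 values discards baseline, and a t test on changes uses baseline with a fixed coefficient of one instead of an estimated one.

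With 15 patients per arm, precision cannot easily be found elsewhere. The adjusted methods use only data that the trial already collects. The paired tests do not fill the gap, because they compare each patient with his or her own baseline and do not estimate endoscopic sleeve gastroplasty (ESG) against laparoscopic sleeve gastrectomy (LSG).

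**Working it through.** **The plan's own figure.** Sample size {14} gives 30 patients, from 85% against 25% resolution with "a confidence level of 99%, a statistical power of 90%, and an assumption of 7% loss". The unpooled normal formula reproduces it:

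n = (z₀.₉₉₅ + z₀.₉₀)² × [p₁(1−p₁) + p₂(1−p₂)] / (p₁−p₂)² = 14.879 × (0.1275 + 0.1875) / 0.36 = 13.02

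That is 14 per arm, 28 in total, and 28/0.93 = 30.1. The calculation contains no stratum or covariate. The checks below use the two-sided 0.05 level of {20a}, with 15 per arm as randomised or 14 per arm after the stated loss (15 × 0.93 = 13.95).

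**Continuous outcomes.** Let r be the correlation between baseline and week 96, with equal variances. The document gives no r, so 0.3 to 0.7 is an assumed range. The variance factors are 1 for the final value, 2(1−r) for the change and 1−r² for ANCOVA. ANCOVA against change is therefore (1−r²)/[2(1−r)] = (1+r)/2.

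| r | ANCOVA / final value | ANCOVA / change |
|---|---|---|
| 0.3 | 0.91 | 0.65 |
| 0.5 | 0.75 | 0.75 |
| 0.7 | 0.51 | 0.85 |

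At r = 0.5 the saving is worth 1/0.75 = 1.33, or about a third more patients. Simulated power with 14 per arm and an assumed 0.8 SD effect, for r = 0.3, 0.5 and 0.7:

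| Diabetes effect | t, final value | t, change | ANCOVA |
|---|---|---|---|
| None | 0.52, 0.54, 0.53 | 0.40, 0.53, 0.75 | 0.54, 0.64, 0.79 |
| 0.8 SD | 0.46, 0.46, 0.47 | 0.36, 0.46, 0.65 | 0.54, 0.63, 0.80 |

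With the 0.8 SD diabetes effect, the true size of the t tests is 0.027 to 0.041, against about 0.05 for ANCOVA.

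**Binary primary endpoint.** The document does not say how response differs by diabetes status, so the rates below are assumptions. I enumerated all outcomes of the four binomials (two strata by two arms) and compared the Pearson chi-square with the CMH test without continuity correction. Simulation gives the same picture. Each cell shows power for chi-square, then CMH, then the gain in points.

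| LSG by stratum vs ESG by stratum | 15 per arm (8+7) | 14 per arm (7+7) |
|---|---|---|
| 85/85 vs 25/25 | 94.5%, 94.3%, −0.2 | 92.2%, 91.9%, −0.3 |
| 69.6/69.6 vs 25/25 | 70.2%, 69.9%, −0.4 | 65.1%, 64.8%, −0.3 |
| 75/65 vs 30/20 | 71.1%, 71.0%, −0.1 | 66.0%, 66.3%, +0.3 |
| 80/60 vs 40/20 | 59.6%, 60.7%, +1.1 | 54.2%, 56.5%, +2.3 |
| 85/55 vs 40/10 | 71.7%, 75.2%, +3.5 | 66.3%, 72.3%, +6.0 |
| 90/45 vs 40/10 | 67.5%, 74.5%, +7.0 | 60.6%, 70.8%, +10.2 |
| 90/50 vs 50/10 | 59.8%, 68.6%, +8.8 | 53.6%, 65.6%, +12.0 |

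(Gains come from unrounded values.)

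**Uneven strata.** For 90/50 vs 50/10 with 15 per arm, the 8.8-point gain falls to 6.8 with an 11+4 split and 4.6 with a 12+3 split.

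**Size with 15 per arm (8+7).** With null rates of 85%/50% by stratum it is 3.8% for chi-square and 4.8% for CMH. At 90%/40% it is 2.4% and 4.6%. With no stratum effect at 70% it is 5.5% and 4.4%.

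**The case against.** The best defence is that nothing here is invalid. When diabetes is prognostic the unstratified test is conservative, so this is a matter of efficiency, not of bias or false positives. That stands.

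A reader might infer that precision is certainly lost on the primary endpoint. The document does not support that. At the response rates in Sample size {14} with no diabetes effect, the stratified test gains nothing. Sizeable gains need large gaps between diabetic and non-diabetic patients within an arm, and balanced strata. The Introduction links insulin resistance to the severity of liver injury, but gives no difference in response.

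A reader might also infer that within-arm p values will stand in for the ESG-versus-LSG comparison. Section {20a} does not plan this: it names between-group tests and says that changes in efficacy endpoints are analysed by randomised group. That wording also suggests that change scores may be compared, so baseline is not wholly ignored. The 25% variance saving is then no constant; it belongs to r = 0.5.

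Finally, an analysis plan that is not shown might add covariates, and ANOVA without listed factors does not exclude a stratum factor. This limits the point without removing it. The article states the tests and defers only the per-protocol exclusions, so the criticism is of a stated choice.

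**Conclusion.** The point holds as one of efficiency. The named tests are valid but do not use the randomisation stratum, and they use baseline poorly or not at all.

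The case is firmest for continuous secondary outcomes. Across assumed correlations of 0.3 to 0.7, ANCOVA removes 9% to 49% of the variance of a final-value test and 15% to 35% of that of a change-score test.

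For the primary endpoint the benefit is conditional. With 15 per arm in balanced strata it runs from a loss of at most 0.4 points of power to a gain of about 7 to 9 points when the strata differ by around 40 points. An even 30-point gap gives 3.5 points with 15 per arm and 6 with 14. Uneven strata reduce the gain. All of these rest on assumed correlations and response rates, because the document gives neither.

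**What to change.** - **Primary endpoint:** CMH test stratified by diabetes, with a Mantel-Haenszel risk difference and 95% confidence interval.
- **Continuous secondary outcomes:** ANCOVA of the week-96 value on arm, baseline value and diabetes stratum, on the log scale where skewed, reporting the adjusted between-arm difference. With 30 patients, add no further covariates.
- **Paired tests:** label them descriptive, and state that conclusions on ESG versus LSG rest on the between-arm estimates.

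The change is one of analysis wording and needs no new data, patients or procedures. It is not free of cost. If diabetes and baseline are not prognostic, a negligible amount of power and a few degrees of freedom are lost. If diabetes status is uneven, the Mantel-Haenszel interval could rest on 3 or 4 patients per arm in the smaller stratum. Its coverage there was not examined here and should be checked before the analysis is fixed.

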#### Criteria for discontinuing or modifying allocated interventions {11b}

In accordance with the revision of the Declaration of Helsinki and current regulations, the patient has the right to withdraw from the study at any time and for any reason, without prejudice to future medical care by his doctor and/or a referral site.

Patients who have withdrawn from the study cannot be included again in the study.

A patient may leave the study for any of the following reasons:
Withdrawal of the informed consent and/or refusal of treatment and/or lack of cooperation.Death of the patient.Decision of the principal investigator and/or sub-investigator in charge, if it is in the patient’s interest to stop the study.

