##### Plans to promote participant retention and complete follow-up {18b}

All patients included in the study will be followed for 96 weeks after the intervention (control vs. experimental) to guarantee the patient’s safety, and all the obtained data will be recorded.

Patients who withdrawn from the study because of the criteria mentioned in section 11b will be followed according to the daily clinical practice of the site.

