#### Methods in analysis to handle protocol non-adherence and any statistical methods to handle missing data {20c}

Not applicable

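### The primary analysis is promised on all randomised patients, but a patient without a week-96 biopsy has no stated outcome, and the exit, follow-up and missing-data sections do not fit that promise

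*Protocol article*

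**What the plan says.** All references are to the protocol article.

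- **Analysis set, {20a}.** "The Intent-to-Treat (ITT) population will include all subjects randomized to treatment", and the primary efficacy analysis is run on that population, "so all randomized subjects will be included in the primary analysis". The test named for qualitative variables is chi-square.
- **Endpoint, Primary outcome.** Both components (fibrosis improvement without worsening of NASH, and NASH resolution without worsening of fibrosis) compare two biopsies. On the second, the text says that "a subsequent biopsy 96 weeks after the procedure should also be obtained".
- **Expected loss, Sample size {14}.** The calculation includes "an assumption of 7% loss".
- **Leaving the study, {11b}.** The first listed reason is "Withdrawal of the informed consent and/or refusal of treatment and/or lack of cooperation". Death and an investigator's decision are the others.
- **Follow-up, {18b}.** The section opens with "All patients included in the study will be followed for 96 weeks after the intervention". It then says that patients who withdrew for the {11b} reasons "will be followed according to the daily clinical practice of the site".
- **Non-adherence and missing data, {20c}.** The whole answer is: not applicable.

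**The concern.** An intention-to-treat analysis needs an outcome, observed or assigned, for everyone randomised. Here the endpoint exists only if a second biopsy is taken, the plan itself expects some patients to be lost, and the item that should say what happens to them is closed. In addition, {11b} treats refusing the procedure as a way out of the study, in the same bullet as withdrawing consent, so patients who might have agreed to be assessed can be lost as well.

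The allocation is open, the patient is told of the intervention after randomisation, and each arm signs its own procedure consent ({16c}, {17a}, {26a}). Refusal after the arm is known is therefore possible. If such patients dropped out of the comparison, it would no longer be the randomised one. With 15 per arm, the handling of one or two patients is visible in the result.

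**Working it through.** **1. The loss is built into the plan's own figure.** Inputs from Sample size {14}: 85% against 25%, two-sided, 99% confidence (alpha 0.01), 90% power, 7% loss. Unpooled normal approximation per arm:

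(2.576 + 1.282)² × (0.85×0.15 + 0.25×0.75) / (0.85 − 0.25)² = 14.88 × 0.315 / 0.36 = 13.02, so 14.

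14 × 1.07 = 14.98, so 15 per arm and 30 in total, as stated. (Dividing instead, 14/0.93 = 15.05, gives 16 per arm and 32.) The 30 therefore already allows for patients who yield no outcome.

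**2. Expected number without an outcome.** 30 × 0.07 = 2.1 in total; 15 × 0.07 = 1.05 per arm. A test on observed outcomes would cover about 28 of 30.

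**3. The sections side by side.**

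| Question | Answer in the article |
|---|---|
| Who is in the primary analysis? | Everyone randomised ({20a}) |
| Will everyone have an outcome? | No, 7% loss is expected ({14}) |
| May a patient who refuses the procedure leave? | Yes ({11b}) |
| What follow-up then? | Routine care ({18b}) |
| When is week 96 for a patient never treated? | Undefined: biopsy and follow-up both count from the procedure (Inclusion criteria, Primary outcome, {18b}) |
| How is a missing biopsy classified? | No rule; {20c} says not applicable |

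**4. Size.** With 15 randomised per arm, r responders and m missing, an arm's response rate lies between r/15 and (r + m)/15. The range of the ESG minus LSG difference therefore has width (m_ESG + m_LSG)/15.

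- One missing outcome: 1/15 = 6.7 points.
- One per arm (about the planned loss): 2/15 = 13.3 points.
- Two per arm: 4/15 = 26.7 points, but this is 4/30 = 13.3% loss, about twice the plan.

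Illustration with assumed counts, one missing per arm and 10 of 14 responding in each: the difference is 0 on observed cases and 0 with missing counted as non-response. The extremes are 10/15 − 11/15 = −6.7 and 11/15 − 10/15 = +6.7 points.

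Illustration with assumed counts and unequal loss (3 of 30, more than planned): ESG 10/15, LSG 8 of 12 biopsied. Observed cases: 66.7% − 66.7% = 0. Missing as non-response: 66.7% − 53.3% = +13.3 points. Missing as response in LSG: 10/15 − 11/15 = −6.7 points. The unstated rule moves the estimate.

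**5. Why one rule alone is not enough.** With equal loss, counting missing as failure multiplies the observed-case difference by the fraction observed. At one per arm this is 14/15 = 0.933. The shrinkage is small at the planned loss, but it goes toward no difference, which suits a hypothesis that ESG does at least as well as LSG.

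**The case against.** The strongest reply is that no section prescribes an observed-cases analysis. {20a} says the opposite, and counting a missing biopsy as non-response would honour it. A separate analysis plan is mentioned and could contain that rule, and the same reply of not applicable is given under many template headings, so it may be filler rather than a decision.

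Much of this stands. A reader might infer that the intention-to-treat analysis is really a completers' analysis; the article does not say so, and that is only what happens if nothing is added. A reader might also infer that patients who leave are denied the biopsy. {11b} only permits leaving, {18b} opens with 96 weeks of follow-up for all, and agreement to the biopsy is an entry criterion. Nor does any section show that refusal will differ between arms or relate to prognosis; that is plausible, not documented.

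What does not stand is treating the matter as mere omitted detail. {20a} defers the per-protocol exclusion list to the analysis plan but not missing data, which {20c} answers. A later rule would have to override {20c}, and it would not repair the exit rule or the clock that starts at a procedure some patients may never have.

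**Conclusion.** The point holds as an inconsistency between {20a}, {14}, {11b}, {18b} and {20c}: the stated primary analysis cannot be carried out on all randomised patients as written, because a patient without a week-96 biopsy has no value on either component and no rule supplies one.

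At about one missing outcome per arm, the treatment difference is open by up to 13.3 points between opposite extremes. This assumes 15 randomised per arm and loss as planned. It is a bound, not a forecast of bias. The 26.7-point figure would need about twice the planned loss and should not be read as the expected effect. The documents do not establish how many patients would refuse, in which arm, or whether the conclusion would change. The correction should be made, and it is inexpensive.

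**What to change.** 1. In {11b} and {18b}, separate not receiving or refusing the procedure from withdrawing consent to follow-up, so that patients who still consent remain in study follow-up.
2. Reconcile the Inclusion criteria, Primary outcome and {18b}, where week 96 runs from the procedure, for randomised patients who never have it. How and when such patients are assessed is for the investigators to settle.
3. Replace the reply in {20c} with a rule: in the intention-to-treat analysis a missing week-96 biopsy counts as non-response for both primary components (fibrosis improvement without worsening of NASH, and NASH resolution without worsening of fibrosis).
4. Add a best-case/worst-case or tipping-point sensitivity analysis for each component, because of the pull toward no difference shown above.

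Cost: slightly lower response rates, a little more analysis, and a protocol amendment. Recruitment opened in June 2020, and under {25} an amendment needs ethics committee approval and a registry update. No additional patients are required.
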